### 4.3 Statistical analysis

All outcomes will be analyzed based on the intention-to-treat principle, in accordance with the randomization allocations described previously. The primary goal of this study is to test the hypothesis that rates of exclusive breastfeeding at 3 months (defined as the feeding of only the infant's mother's milk for at least 2 weeks prior to collected outcome) will be higher in the group of women attending the post-partum clinic, as compared to those under standard of care. For comparison between intervention and control arms we will employ a generalized estimating equation multivariable regression model to account for prognostic risk factors that have not been sufficiently balanced by randomization. Group and individual level covariates will be included in the model, with recruitment site as the clustering unit to allow for inference at the individual level. This design will also investigate the effect of demographic

drivers such as maternal age, education, parity, etc., on the primary outcome, producing both crude and adjusted risk estimates and their 95% confidence intervals.

Secondary outcomes will be collected by studying the medical data (such as rates of hyperbilirubinemia and self-efficacy) that will be entered in the database by the research staff. This data will be compared across case and control groups using the Pearson Chi-squared, Student's t, or Fisher's exact test, depending on their observed frequencies. We will also compare the statistics and outcomes from the present study with baseline estimates from phase 1. The answers women provide through their questionnaires and surveys will be the main instruments for determining exclusive breastfeeding rates and their behavioral and emotional measurements. For the cost-effectiveness analysis, direct and indirect costs for the intervention and control groups will be compared regarding use of resources (e.g., clinic visits, physician visits, Emergency Department visits, hospital readmission, and indirect cost).

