### 3.2 Events prior to hospital discharge

#### 3.2.1 Data collection

Once consent has been obtained, the research team will collect information about delivery (mode of delivery and date and time of birth), obstetrical (previous pregnancies, parity) history, and information on the baby (gender, ethnicity, gestational age at birth, birth weight, Apgar score, bilirubin levels (TCB [trans cutaneous bilirubin] and/or TSB [total serum bilirubin], whether supplementation was given and date and time of discharge) from the hospital chart.

Contact information will be recorded in the study master log. As well, the OHIP number will be recorded in the master log to eventually allow the linkage of the dataset to ICES administrative data.

Upon confirmation by the pediatrician, the obstetrician, the family physician, and/or the midwife in attendance that the mother and baby have no counter-indication for early discharge, the research team will proceed to randomize the participant.

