#### 3.2.2 Randomization

Study participants will be randomly assigned to either the intervention (discharge with follow-up at the breastfeeding clinic) or the control (standard of care) groups via a 2:1 allocation ratio, with group designations being determined after the patient is enrolled and informed consent is obtained. Stratification will be used to improve allocation balance by site of recruitment and parity of participants. Group designation is given from a randomization list, which will be generated using a permuted randomized block design, with permuted blocks of sizes 3, 6, and 9 units, prior to study initiation. This list is then entered directly into REDCap's group allocation component which assigns group placement based on the inputted randomization list at the time of initial data entry, all the while blinding the study researchers, recruiters, and participants to the randomization allocations prior to patient enrollment and data collection. The study staff will then inform the participant of their randomization group. Rather than occurring at the time of consent, randomization will be delayed until confirmation by the nurses and/or attending physicians that the participant is indeed a candidate for discharge at approximately 24h ( $\pm$  12) after vaginal or 48h ( $\pm$  12) after C section delivery.

[figure not shown]

**FIGURE 1. Schematic diagram showing the two possible outcomes after randomization.** In the case of this breastfeeding study, the participants may be assigned the standard-care or the post-partum clinic option.

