### 3.5 Follow-up surveys at 2 weeks, 1 month, 3 months and 6 months after hospital discharge

Participants will be contacted by email or by phone to complete the following:

- At 2 weeks:
  - **A questionnaire assessing breastfeeding complications**, developed for this study
  - **Breastfeeding Self Efficacy Scale (BSES-SF)**. This is a 14-item self-report instrument developed to measure breastfeeding confidence 
  - A questionnaire to assess the **access to community resources**, the rate of readmission of the babies and the level of satisfaction of mothers with the breastfeeding support received.
  - A questionnaire to determine the **rate of exclusive breastfeeding**. Participants will be asked to answer question on the methods used to feed their babies in the past 24 h hours and in the past two weeks. Exclusive breastfeeding will be as defined as the feeding of only the infant's mother's milk for at least 2 weeks prior to collected outcome.
- At 3 weeks only (by phone by a nurse from Ottawa Public Health)
  - **Edinburgh Postnatal Depression Scale**. This is a 10-item screening tool to identify postpartum depression at the time of its administration . A score of 13 or higher on the EPDS is considered indicative of postpartum depression and a score of 10 to 12 is indicative of being at risk for postpartum depression (see section 3.6).
- At 1 month:
  - **Breastfeeding Self Efficacy Scale (BSES-SF)**. This is a 14-item self-report instrument developed to measure breastfeeding confidence 

- A questionnaire to assess the **access to community resources**, the rate of readmission of the babies and the level of satisfaction of mothers with the breastfeeding support received.
  - A questionnaire to determine the **rate of exclusive breastfeeding**. Participants will be asked to answer question on the methods used to feed their babies in the past 24 h pours and in the past two weeks. Exclusive breastfeeding will be as defined as the feeding of only the infant's mother's milk for at least 2 weeks prior to collected outcome.
  - **Socio-demographics survey**. This survey was developed using questions and categories used in the Public Health Agency of Canada survey “What Mothers Say: The Canadian Maternity Experiences “
- At 3 months:
    - **Breastfeeding Self Efficacy Scale** (BSES-SF). This is a 14-item self-report instrument developed to measure breastfeeding confidence

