| Maternal care and neonatal care (jaundice screening using transcutaneous bilirubinometer and weight gain assessment) at the clinic. |   | X |   |     |     |     |     |     |
| Breastfeeding support at clinic                                                                                                     |   | X | X |     |     |     |     |     |
| Additional medical care at clinic                                                                                                   |   |   | X |     |     |     |     |     |
| Collection of medical data from visits at clinic                                                                                    |   | X | X |     |     |     |     |     |
| Demographics survey                                                                                                                 |   |   |   |     |     | X S |     |     |
| Edinburgh Postnatal Depression Scale                                                                                                |   |   |   |     | X S | X S |     |     |
| Breastfeeding local complications survey                                                                                            |   |   |   | X S |     | X S |     |     |
| Breastfeeding survey                                                                                                                |   |   |   | X S |     | X S | X S |     |
| Use of resources survey                                                                                                             |   |   |   | X S |     | X S | X S |     |
| Self-efficacy survey                                                                                                                |   |   |   | X S |     | X S | X S |     |
| Mother Satisfaction Survey                                                                                                          |   |   |   |     |     |     | X S |     |
| 6 month follow up survey                                                                                                            |   |   |   |     |     |     |     | X S |

Index: X = Women assigned to the breastfeeding clinic program will be completing these events

S = Women assigned to the standard care will be completing these events

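### Section 4.3 lets observed imbalance decide the covariates and ranks neither the crude nor the adjusted estimate, and education, a named covariate, is collected only at one month

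*Protocol*

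**What the plan says.** Protocol section 4.3 compares the arms with a generalized estimating equation regression and gives its purpose: "to account for prognostic risk factors that have not been sufficiently balanced by randomization". It adds that "Group and individual level covariates will be included in the model", makes recruitment site the clustering unit, and says the analysis will also look at "drivers such as maternal age, education, parity, etc., on the primary outcome", "producing both crude and adjusted risk estimates and their 95% confidence intervals". It gives no criterion for insufficient balance, leaves the covariate list open, and ranks neither estimate above the other.

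On design, section 3.2.2 states: "Stratification will be used to improve allocation balance by site of recruitment and parity of participants".

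On data, section 3.2.1 says that after consent "the research team will collect information about delivery (mode of delivery and date and time of birth), obstetrical (previous pregnancies, parity) history", along with details of the baby, from the hospital chart. Maternal age and education are not in that list. Section 3.5 places the socio-demographic survey under the one-month contact ("This survey was developed using questions and categories used in the Public Health Agency of Canada survey"). The calendar in section 3.8 marks "Demographics survey" in the Day 30 column only, for both arms, while randomisation stands in the Day 0 column.

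**The concern.** In a properly randomised trial any baseline imbalance is due to chance. The reason to adjust is that a covariate predicts the outcome or was used to stratify, and both are known before any data arrive. A rule that waits to see which factors look unbalanced has three consequences.

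- The primary model is not known until the data are in.
- Precision from strong but balanced predictors is given up.
- With an open list and two unranked estimates, nothing in the protocol settles which result answers the primary question.

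The rule also sits badly with the design. Stratification tends to balance site and parity, so a rule based on residual imbalance gives no reason to adjust for them.

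The timing of the survey adds a practical difficulty. Education is named as a covariate, yet its only scheduled collection comes about a month after randomisation, near the end of the clinic period. A woman who misses that contact but answers at 3 months has a primary outcome and no education value.

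**Working it through.** The protocol states no figure for this point, so there is none to reproduce. The sizes below are illustrations under stated assumptions.

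**1. Which covariates are tied to Day 30**

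| Variable | Source in the protocol | Before randomisation? |
|---|---|---|
| Site, parity | Stratification factors (3.2.2); parity also in the chart (3.2.1) | Yes |
| Mode of delivery | Hospital chart (3.2.1) | Yes |
| Maternal age | Not in the chart list, but eligibility requires at least 18 years at enrolment (2.5) | Must be established, not listed as recorded |
| Education | One-month survey only (3.5, 3.8) | No |

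**2. Power given up by choosing on imbalance**

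Simulation A assumed 391 women, 2:1 allocation stratified by parity, parity plus four moderately prognostic covariates, a 13-point effect, and 2,500-4,000 runs. The 13 points are an assumption and not a protocol figure. Ranges run across settings; differences match low end with low end and high end with high end.

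- Power: crude 79.8-81.0%, prespecified adjustment 81.2-84.8%, imbalance-picked 80.3-82.1%.
- Prespecified over crude: 81.2 − 79.8 = 1.4 and 84.8 − 81.0 = 3.8 points.
- Imbalance-picked over crude: 80.3 − 79.8 = 0.5 and 82.1 − 81.0 = 1.1 points.
- Forgone: 81.2 − 80.3 = 0.9 and 84.8 − 82.1 = 2.7, so roughly 1 to 3 points.

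**3. Type I error at nominal one-sided 5%**

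- Simulation A: crude 4.5-4.6%, adjusted 4.7-5.1%, significant on either 5.3-6.0%.
- Simulation B (131 against 260 women, six assumed covariates, linear probability model, 6,000 runs per setting): imbalance-picked alone 3.9-5.1%, full prespecified adjustment 4.8-5.4%, most favourable of crude, full and imbalance-picked 5.9-8.5%.
- Simulation standard error in B: √(0.05 × 0.95 / 6000) = 0.0028, about 0.3 points. In A, with 2,500-4,000 runs, it is about 0.3-0.4 points, so the 5.3% end is close to nominal.

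Imbalance selection alone shows no inflation. The excess comes from free choice among results.

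**4. Women lost if education enters a complete-case model**

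Inputs from section 4.1: 154 control and 306 intervention, 15% attrition, control rate 50%.

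- Women with a 3-month outcome: 154 × 0.85 = 130.9 and 306 × 0.85 = 260.1, in total 391.
- Assume a fraction m of these lacks the Day 30 survey. The documents give no value for m.
- One-sided power = Φ{[(p₂ − p₁) − 1.645 √(p̄(1 − p̄)(1/n₁ + 1/n₂))] / √(p₁q₁/n₁ + p₂q₂/n₂)}, with p̄ the rate pooled over both arms.
- For m = 0 and 50% against 65%: p̄ = 0.600, the null standard error is 0.0525 and the alternative one 0.0528. Then (0.15 − 1.645 × 0.0525)/0.0528 gives about 1.21, and Φ = 88.6%.

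| m | Women kept | Power, 50% v 65% | Power, 50% v 57.5% |
|---|---|---|---|
| 0 | 391 | 88.6% | 40.6% |
| 5% | 371 | 87.2% | 39.2% |
| 10% | 352 | 85.5% | 37.8% |
| 20% | 313 | 81.8% | 35.0% |

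Both effects are shown because section 4.1 states a 15% relative difference (57.5%), while its 200 per group is close to what an absolute 15 points needs (198, one-sided, continuity-corrected). That mismatch is a separate matter. Neither column counts any precision gained from the adjustment itself.

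**The case against.** The strongest reply is that covariate lists, the choice of primary estimate and the handling of missing covariates commonly sit in the SAP, which is not at hand. This stands for missing covariates. It does not stand for the selection rule: section 4.3 states one, and an SAP that fixed covariates whatever their balance would depart from it. Nor can an SAP recover data that were not collected at baseline.

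Several stronger readings are tempting but unsupported.

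- **The stratifiers are discarded.** Section 4.3 keeps site as the clustering unit, names parity as a driver and says covariates will be included. What can be said is that neither is committed to the treatment-effect model, and clustering on site is not adjusting for it.
- **Up to 69 women are affected.** 460 × 0.15 = 69 is the planned attrition. Women lost by 3 months have no primary outcome, so a missing covariate removes nobody further. Nor is 15% a ceiling on Day 30 non-response.
- **Early non-responders are excluded.** That needs a complete-case model with survey covariates. The protocol does not state one, it claims intention to treat, and the crude estimate is unaffected.
- **The late covariate is contaminated by treatment.** Education hardly changes in 30 days. The problem is missingness.
- **Response will differ by arm.** Only clinic women have visits and travel reimbursement, but survey contacts, the email reminder and the telephone option apply to both arms. A difference is possible, but nothing in the documents shows it.

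It is also fair to say that the measured effects are small and rest on invented covariates.

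**Conclusion.** The point holds as a cheap improvement to a rule that the protocol fixes badly. It does not show that the primary result would be invalid. Section 4.3 makes adjustment depend on observed balance, leaves the stratification factors uncommitted in the treatment-effect model and names no primary estimate.

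Under assumed covariates the cost is roughly 1 to 3 points of power. If crude and adjusted results may be chosen between freely, one-sided error rises to about 5.3-6.0%; the 5.9-8.5% figure supposes deliberate choice of the best of three analyses. A reader might infer that picking covariates by imbalance inflates type I error by itself. The simulations do not support that.

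The timing fault is narrower: among the covariates that section 4.3 names, education is the one clearly tied to Day 30. An assumed 5-20% non-response among about 391 women would cost a complete-case model 20 to 78 of them. The true rate cannot be had from the documents.

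**What to change.** In section 4.3:

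- Delete the clause that ties adjustment to observed imbalance.
- Name one primary estimate: the treatment effect adjusted for site and parity plus a short fixed list of variables known before randomisation, for example maternal age and mode of delivery, whatever their observed balance.
- Label the crude estimate supportive.
- With site entered as a covariate, its role as clustering unit should be settled at the same time.

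In sections 3.2.1, 3.5 and 3.8:

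- Add maternal age to the data recorded before randomisation.
- Move the socio-demographic survey from Day 30 to enrolment, after consent and before allocation, in both arms. Section 3.2.2 already delays randomisation beyond consent, which leaves a place for it.

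The cost is a change of wording and the move of one existing form, made before enrolment starts. The downside is some extra questionnaire time in hospital. The documents do not give the form's length; section 3.5 gives only about 40 minutes for a whole telephone interview at each contact.

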## 2.5 Inclusion criteria:

Mothers having delivered a baby at The Ottawa Hospital - General or Civic Campus:

1. Who are  $\geq 18$  years at the time of enrollment
2. Who are any parity, with a singleton infant born  $> 36 + 6$  weeks of Gestational Age
3. Who have no medical counter indication for discharge at 24 ( $\pm 12$ ) hours post vaginal delivery or 48 ( $\pm 12$ ) hours post C-section delivery and for which the physician (family physician or obstetrician) has agreed that the mother is eligible
4. Who are breastfeeding and intend to breastfeed their baby upon discharge
5. Whose infant is healthy with no counter indication for discharge at 24 ( $\pm 12$ ) hours post vaginal birth or 48 ( $\pm 12$ ) hours post C-section birth and for which the physician (family physician or paediatrician) has agreed that the infant is eligible
6. Who can be contacted by phone or E-mail after hospital discharge

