## 4 Statistics

### 4.1 Sample size

Based on an estimated 50% rate of exclusive breastfeeding at 3 months in the control group, 200 patients per group will be needed to detect a 15% relative difference in the intervention group ( $\alpha=0.05$ ,  $\beta=0.9$ , one-sided test). Assuming an attrition rate of 15% (i.e. loss to follow up, unsuitability, or other unanticipated events), we set a target of **230 participants per group** making a total of **460** women. Accounting for the logistical concern of making full use of the nursing staff, lactation consultants, and family physicians at the clinic, we decided to apply a 1:2 ratio for control to intervention allocations and determined that 154 and 306 patients are needed for the control and intervention groups respectively (maintaining significance level, power, and effect size).

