### 4.2 Feasibility

It is estimated that the number of deliveries at our catchment hospitals is approximately 3200/year at each site. Assuming that at least 55% of those women qualify for the study, there will be an average of 10 eligible patients/day during the study period. We anticipate a response rate of 50% and expect to

enroll an average of 5 women per day, 6 days a week. The anticipated total number of patients who qualify to be enrolled in the study is 5 patients x 6 days x 4 weeks x 5 months = 600 (Figure 2). Therefore, even with unexpected events or lower than expected daily recruitment capacity our final estimated sample sizes should be sufficient to recruit enough participants for the on-time completion (8 months) of the study.

Figure 2: Flow chart of expected study participant recruitment

[figure not shown]

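### The primary GEE clusters on recruitment site, but there are only two sites and women are randomised individually within them; with the usual robust standard error the one-sided error would be about 23%, not 5%

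*Protocol*

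**What the plan says.** Protocol section 4.3 compares the arms with a "generalized estimating equation multivariable regression model", "with recruitment site as the clustering unit to allow for inference at the individual level". The model is also to adjust for prognostic factors, among them maternal age, education and parity, "producing both crude and adjusted risk estimates and their 95% confidence intervals".

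Three other places fix the design that this model has to fit:

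- Section 2.5 recruits "Mothers having delivered a baby at The Ottawa Hospital - General or Civic Campus", so there are two sites. Section 4.2 agrees, with deliveries put at "approximately 3200/year at each site".
- Section 3.2.2 allocates individual women "via a 2:1 allocation ratio" and adds: "Stratification will be used to improve allocation balance by site of recruitment and parity of participants".
- Section 4.1 sizes the trial at alpha 0.05 with a "one-sided test".

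The protocol does not name the variance estimator (robust or model-based), the working correlation, any small-sample correction or the reference distribution.

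**The concern.** The usual GEE standard error is the robust, or sandwich, estimate. It measures how much the clusters' score contributions vary, and it is justified when clusters are many. With two clusters those contributions must sum to zero, so the whole estimate rests on a single contrast between the two campuses. If the campuses happen to give similar treatment effects, the standard error is nearly zero; if they happen to differ, it is large. Adding covariates or a site term does not cure this.

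The clustering is also not needed. Both arms occur within each campus, so site is a stratification factor and not a unit of allocation. Individual randomisation already allows inference at the individual level, which is the reason section 4.3 gives for the clustering.

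At stake are the p-value and confidence interval for the primary outcome, and so the risk of concluding that the clinic works when it does not.

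**Working it through.** **Inputs.** Two sites (section 2.5) of about equal size (section 4.2). 2:1 allocation within site and parity strata (section 3.2.2). One-sided alpha 0.05, control rate 50%, planned arms of 154 and 306, 15% attrition (section 4.1). Evaluable women: 460 × 0.85 = 391. The nominal 0.05 is the only error rate that the plan states, so it has no operating characteristic for this model to reproduce. The closed form below does not depend on the sample size.

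**Closed form, two equal sites, no true effect, uncorrected robust SE.** Let b1 and b2 be the treatment effects estimated at the two sites, independent and normal with mean 0 and variance s².

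1. The pooled estimate is (b1 + b2)/2.
2. The sandwich variance is [(b1 − mean)² + (b2 − mean)²]/4 = (b1 − b2)²/8, so SE = |b1 − b2|/(2√2).
3. The Wald statistic is z = √2 × (b1 + b2)/|b1 − b2|. The sum and the difference are independent with equal variance, so z is √2 times a Cauchy variable.
4. The one-tail probability beyond c is 0.5 − arctan(c/√2)/π.

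| Rule | c | Closed form | Simulated |
|---|---|---|---|
| One-sided 0.05 (section 4.1) | 1.645 | 22.6% | 21–25% |
| One tail beyond 1.96 | 1.96 | 19.9% | 19–22% |
| Two-sided 0.05 (95% CI excludes no effect) | 1.96 | 39.8% | 38–43% |

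The last row means that a nominal 95% interval covers about 100 − 39.8 = 60% of the time.

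**How unstable the SE is.** The correct SE of the pooled estimate is s/√2. The robust SE is s|Z|/2 with Z standard normal, so their ratio is |Z|/√2: 5th percentile 0.063/1.414 = 0.04, median 0.674/1.414 = 0.48, 95th percentile 1.96/1.414 = 1.39. The simulations agree (about 0.04, 0.46 and 1.4).

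On the log odds ratio scale, with 154 × 0.85 = 130.9 and 306 × 0.85 = 260.1 evaluable women and a 50% rate in both arms, the correct SE is √(4/130.9 + 4/260.1) = 0.21. The robust SE would then run from about 0.01 to 0.30, with a median of about 0.10.

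**Simulation.** Logistic GEE with no effect, 391 or 460 women, site split 50:50 or 65:35, with and without covariates, a site term and a site effect, 3000 runs each. A separate check with a standard GEE routine, under independence and exchangeable working correlation (1500 runs each), gave 22–24% at one-sided 0.05 and 39–40% two-sided.

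**Alternatives, no true effect, nominal 0.05.**

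| Analysis | One-sided | Two-sided |
|---|---|---|
| Site-clustered GEE, model-based SE | 3.9–5.5% | 4.1–6.4% |
| Site-clustered GEE, robust SE, t reference with 1 df | 6–8.5% | 7–8% |
| Individual-level logistic model, site as fixed covariate, model-based SE | about 5% | 4.3–5.7% |

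**The case against.** The strongest reply is that section 4.3 names a model and a clustering unit, but no variance estimator. A GEE can report model-based standard errors, and with those the same sentence gives a test close to its nominal level. The variance estimator, working correlation and small-sample correction are details that a protocol commonly leaves to the SAP, which is not at hand.

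This stands as far as the error rates go. A reader might infer that the primary test, as written, has a false-positive rate of 20% to 40%. The documents do not support that: the inflation needs an uncorrected robust SE together with a normal reference, and the protocol commits to neither. A figure of about 20% would also be the wrong one for the stated one-sided 0.05. It belongs to the single tail beyond 1.96; at 1.645 the figure is about 23%.

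The reply does not rescue the clustering unit. The protocol itself fixes that, no other section qualifies it, and it treats a two-level stratification factor as a cluster. If the SAP chose the model-based SE, the test would be sound, but the clustering would then have served no purpose.

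A reader might also infer that the plan needs a particular effect measure or a different model family, such as modified Poisson. These are choices for the analyst and are not needed to cure the defect. Section 4.3 already promises crude and adjusted risk estimates and already lists parity as a covariate.

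**Conclusion.** The point holds in a conditional form. Recruitment site is the wrong clustering unit for an individually randomised trial at two sites, and the protocol states it for the primary outcome. If the usual default is followed (uncorrected robust SE, normal reference), the false-positive rate is about 23% at the stated one-sided 0.05 and about 40% two-sided, and the 95% intervals are invalid. If a model-based SE is used, the error stays near 5%. The protocol leaves open which applies.

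The closed form assumes two sites of equal size and approximately normal site-level estimates. The simulations show that an unequal split, covariates or a site term change the rates little.

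**What to change.** In section 4.3, remove recruitment site as the clustering unit. State that the primary outcome will be analysed with an individual-level binary regression (logistic, for example) with treatment, site and parity as fixed covariates, parity and site being the stratification factors, and with model-based or individual-level robust standard errors. The other planned covariates can stay.

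The cost is one sentence in the protocol, carried into the SAP. Data collection, randomisation and sample size do not change.
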